## Abstract

**Introduction:** Fever of unknown origin (FUO) and hemodynamic instability are complications that develop after cardiac surgery combined with cardiopulmonary bypass (CPB) for heart disease. Patients who develop fever with hemodynamic instability after cardiac surgery may have systemic inflammatory response syndrome or sepsis. Cardiopulmonary bypass (CPB) is a technique that temporarily takes over the function of the heart and lungs during cardiac surgery. Recent reports suggest that early bloodstream infections of patients undergoing CPB are due to gram-negative bacteria that are present in the intestinal flora. The theory of intestinal flora translocation has growing evidence. Intestinal ischemia-reperfusion that occurs during cardiac surgery with CPB will induce a systemic inflammatory reaction and may cause intestinal flora translocation. Does this systemic reaction cause sepsis? We therefore propose this protocol to determine whether the changes in the intestinal flora in patients after cardiac surgery with CPB are related to sepsis.

**Methods and Analysis:** This study is a prospective observational case–control study to analyze the variation in the intestinal microflora and metabolites in patients undergoing cardiac surgery with CPB and to observe the outcomes of patients with routine clinical interventions. The control group will include healthy people without intestinal illness. Feces and blood samples will be acquired 1 day before cardiac surgery and within 24–72 h after cardiac surgery, and will be used for genomics and metabolomics analyses. Demographic data describing age, sex, main diagnosis, and past medical history and data related to the CPB time and application of antibiotics are available. Sequential (sepsis-related) organ failure assessment, infection-related laboratory items, infection site, and pathogenic microorganisms, and nutrition, and gastrointestinal function assessment are additionally recorded. Group analysis of data will be conducted according to the outcomes (sepsis vs. non-sepsis and survivors vs. non-survivors).

**Ethics and Dissemination:** This protocol has been ethically approved by the Ethics Committee of Peking Union Medical College (ID: ZS-1612). Informed consent will be obtained before subject enrolment, and data will be stored in a secured database. The results will be submitted to international peer-reviewed journals and presented at international conferences.

**Trial Registration Number:** NCT04032938.

## Introduction

Complications after cardiac surgery are important factors that increase postoperative mortality after surgery (1). A prospective cohort study involving 4,446 consecutive patients undergoing cardiac surgery showed that there are some critical postoperative complications after cardiac surgery, including infection, renal failure, pulmonary complications, gastrointestinal complications, and multiorgan failure (2). The results showed that the in-hospital mortality was 3%, the postoperative renal failure incidence was 10%, the pulmonary complication rate was 32%, the gastrointestinal complication rate was 8%, the neurological complication rate was 7%, and the multiorgan failure rate was 2%. After undergoing cardiac surgery, patients are usually critically ill and require intensive care. Interestingly, we know from experience that some patients develop fever and hemodynamic instability after cardiac surgery without definitive etiological evidence. Previous studies have shown that systemic inflammatory response syndrome and postoperative fever are complications that develop after cardiac surgery (3, 4). We speculate that fever of unknown origin (FUO) and hemodynamic instability are related to systemic inflammatory response syndrome or sepsis. However, they may not be. The use of CPB or extracorporeal life support (ECLS) to support a patient during an intraoperative thoracic surgery is common, and cardiopulmonary bypass (CPB) is one of the risk factors for infection in patients undergoing cardiac surgery (5). On the one hand, it is reported that most of the early bloodstream infections of patients undergoing CPB are caused by gram-negative bacteria, which are commonly present in the intestinal flora (6). This finding indicates a relationship between the intestinal flora and infection or sepsis. On the other hand, the CPB process and duration of CPB determine the severity of organ ischemic injury. Intestines, as an ischemia-sensitive organ, will allow translocation of bacteria and endotoxins to the bloodstream (7). Therefore, the intestines play a role in postoperative sepsis or infection.

There is growing evidence that microbiomes play an indispensable role in human health and disease. Meanwhile, a lot of progress has also been made in association studies between disease and intestinal metabolites. As early as the later part of the nineteenth century, researchers found that peritonitis could result from the passage of bacteria from organs adjacent to the peritoneal cavity. The “gut origin of sepsis” became a theory of interest to clinicians (8). The theory of intestinal flora translocation has gradually emerged. Dickson et al. found the lung bacteria of patients with ARDS, which is correlated with systemic inflammation translocated from the intestine (9). Singer et al.'s research in mice and patients who died of sepsis suggests that bacterial translocation could be associated with sepsis in acute neuroinflammation (10). Other studies found that a ratio of Bacteroidetes to Firmicutes (B/F ratio) of >10 or <0.10 in the gut microbiota may suggest a high risk of death (11). We hypothesized that, except for iatrogenic infections, endogenous bacterial translocation after CPB is a possible mechanism of early sepsis or septic shock in these patients. The use of intestinal microecological studies and metabolite studies can help determine whether changes in the intestinal flora and metabolites after cardiac surgery with CPB are associated with sepsis. This research method has become very mature in clinical research. There are a series of studies on the host microbiota with neurologic, metabolic, cardiovascular, or gastrointestinal disorders (12–16). Studies on the association between disease and intestinal metabolites have also made essential progress. We hypothesize that sufficient information related to the pathogenesis of sepsis can be obtained from studies on intestinal microecology and metabolites.

This study will identify the variation in the gut microbiota and host metabolite profiles of patients after undergoing cardiac surgery with CPB. The changes in the intestinal flora in patients with sepsis and patients with worse outcomes will be analyzed emphatically. Combined with clinical data, the possible pathogenesis of FUO and patients with hemodynamic instability and their association with infection will be analyzed. This study may also indicate whether the phenomena of FUO and hemodynamic instability are attributed to sepsis or a purely inflammatory response.

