## Method and Analysis

### Study Design

This protocol is designed as a prospective observational case–control study in patients who underwent cardiopulmonary bypass (CPB) due to cardiac surgery. Thirty healthy persons aged between 18 and 85, without digestive system disease, will be selected as the control group. The case group will include patients admitted to the intensive care unit (ICU) after cardiac surgery with CPB, which is performed by the Department of Cardiac Surgery of Peking Union Medical College Hospital. The patients enrolled should be divided into two groups according to their outcomes: one group of non-sepsis patients and the other group of sepsis patients after cardiac surgery. Sample collection will be terminated when each group receives 30 cases. These 60 cases will be regarded as the case group. Additionally, all the patients we observe will be further divided into survivors and non-survivors based on 28-days survival. Feces and blood samples will be obtained at certain time points (Figure 1).

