#### Grouping by Outcomes

The primary outcome is patients with cardiovascular surgery with CPB and healthy people.

The secondary outcomes are as follows.

After sample collection, the case group will be selected and divided into two groups according to their clinical outcomes.

Sepsis group (sub grouped by suspected or documented infection) and non-sepsis group;Survivors and non-survivors based on the 28-days survival.

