### Multi-Omic Data Analysis Plan

The data will be analyzed according to the case and control groups, sepsis and non-sepsis groups, and survivor and non-survivor groups, or some other classifications based on the pathophysiology.

Metagenomic and metabolomics statistical analysis will be performed using commercial software. To account for dependencies in repeatedly measured observations within a subject, a linear mixed-effect model will be used to assess the differences between the case group and the control group. Statistical analysis will be performed using SPSS (version 22, SPSS, Chicago, IL). A two-sided significance level of 0.05 will be used for statistical inferences. Combining principal component analysis (PCA), partial least squares discriminant analysis (PLS-DA), and orthogonal partial least square discriminant analysis (OPLS-DA), different metabolite profiles will be identified.

Receiver operating characteristic (ROC) analysis will be conducted to evaluate the utility of the potential biomarkers selected. Multivariate logistic regression analysis will be used to show the correlation between each factor and prognosis and changes in intestinal flora. A *p* < 0.05 will be considered statistically significant.

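### A survivor versus non-survivor analysis and a multivariable logistic model of prognosis are planned, but nothing secures enough deaths among the 60 cases to support them

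*Protocol article*

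**What the plan says.** The Study Design section of the protocol article fixes the case group by sepsis status: "Sample collection will be terminated when each group receives 30 cases", and "These 60 cases will be regarded as the case group". It then adds that "all the patients we observe will be further divided into survivors and non-survivors based on 28-days survival".

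Grouping by Outcomes lists the same split among the secondary outcomes, within the case group: "Survivors and non-survivors based on the 28-days survival". The Discussion also ties the survival outcome to sixty enrolled patients.

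The Multi-Omic Data Analysis Plan names survivors and non-survivors as one of its contrasts. It also plans ROC analysis of selected biomarkers, without naming the outcome to be classified, and states: "Multivariate logistic regression analysis will be used to show the correlation between each factor and prognosis". Two-sided 0.05 is the only significance threshold.

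The only mortality rate in the document is in the Introduction, where it describes "A prospective cohort study involving 4,446 consecutive patients undergoing cardiac surgery" and reports that "the in-hospital mortality was 3" percent. It is background and is not used as a planning assumption.

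**The concern.** Sepsis has a recruitment quota and death has none. The number of deaths is therefore left to chance, while the article already fixes an inferential method for an outcome that may have only a handful of events.

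With few deaths, a model with several factors fits noise. Its odds ratios are unstable, and it can fail to converge through separation when deaths are very few and covariates many. Metagenomics and untargeted metabolomics will also supply many candidate features, so some will appear to discriminate deaths well by chance. The risk is that the paper reports prognostic markers of death that cannot be reproduced.

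**Working it through.** The protocol gives no expected number of deaths, power or effect size, so there is no planned figure to reproduce.

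**Inputs from the document.** 60 cases, 30 septic and 30 non-septic (Study Design); 3% in-hospital mortality in consecutive patients (Introduction); two-sided 0.05 (Multi-Omic Data Analysis Plan).

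**Step 1: deaths at the unselected rate.** 60 × 0.03 = 1.8. Under Binomial(60, 0.03), P(0) = 0.97^60 = 0.161 and P(2 or fewer) = 0.161 + 0.298 + 0.272 = 0.731.

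**Step 2: allow for the sepsis quota.** Every added input here is an assumption.

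- Septic mortality 10% to 30%, non-septic 3%: 30 × 0.10 + 30 × 0.03 = 3.9, up to 30 × 0.30 + 30 × 0.03 = 9.9.
- Alternatively, keep 3% overall. Let s be the sepsis share in unselected patients and f the share of deaths that occur in septic patients. Deaths = 30·f·0.03/s + 30·(1−f)·0.03/(1−s). For f from 0.5 to 1:
  - s = 30% gives 2.1 to 3.0
  - s = 20% gives 2.8 to 4.5
  - s = 10% gives 5.0 to 9.0
  - s = 5% gives 9.5 to 18, which requires septic mortality of 30% to 60%

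A reasonable range is about 2 to 10 deaths, with 18 as a high case.

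**Step 3: what that supports.** At the customary 10 events per variable, 2 to 9 deaths support no covariate (0.2 to 0.9), 10 support one, and 18 support at most one (1.8).

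The Hanley-McNeil variance for an AUC A with k deaths and m = 60 − k survivors is [A(1−A) + (k−1)(Q₁−A²) + (m−1)(Q₂−A²)]/(km), where Q₁ = A/(2−A) and Q₂ = 2A²/(1+A). At A = 0.80, Q₁ = 0.667 and Q₂ = 0.711. For k = 2 this is (0.16 + 0.027 + 4.053)/116 = 0.0366, so SE = 0.191 and the 95% half-width is 1.96 × 0.191 = 0.37. With 4 deaths, SE = 0.136 and the half-width is 0.27.

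Power is from the noncentral t for k versus 60 − k patients:

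| Events | Power, 0.8 SD difference | Difference detectable at 80% power | AUC 0.80, 95% half-width |
|---|---|---|---|
| 2 | 19% | 2.05 SD | 0.37 |
| 5 | 39% | 1.33 SD | 0.24 |
| 9 | 59% | 1.03 SD | 0.18 |
| 30 (sepsis) | 86% | 0.74 SD | 0.11 |

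**Step 4: separation and chance findings.** These use 60 patients and features unrelated to outcome. With 2 deaths and independent continuous covariates, simulated complete separation occurs in a few percent of models with 3 covariates, about 20% with 5 and about 69% with 8. With 4 deaths and 5 covariates it is about 2% or less, and with 9 deaths it was not seen. For a single null feature, the chance of an AUC of 0.90 or more in either direction is 4.7% with 2 deaths and 0.4% with 4. Per 1,000 features (an illustrative number) that is about 47 and 4.

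**The case against.** Several objections have force.

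- **The 3% does not transfer.** It is in-hospital mortality in consecutive patients. The study outcome is 28-day survival in a sample that is half septic by quota. A reader might infer that the protocol's own figure implies about two deaths. It does not: 1.8 is close to a floor if sepsis raises mortality and its natural share is below 50%. This stands, and it is why a range is used.
- **Separation is not inevitable.** A reader might infer that the model cannot be fitted at all. The simulations do not support that, and the protocol gives no number of covariates. Overfitting and imprecision are the general problem, and separation is the extreme case.
- **ROC is not tied to death.** The outcome is unnamed and could be sepsis, 30 versus 30. The AUC figures therefore apply only if ROC is used for death. Prognosis is also undefined and could be read as sepsis, but survival is the other outcome the plan names and nothing excludes it.
- **More than 60 patients may be observed.** Study Design allows this reading, although Grouping by Outcomes and the Discussion point to the 60. It changes little. Reaching 30 septic cases at sepsis shares of 30%, 20% and 10% means observing about 100, 150 and 300 patients, which at 3% is 3, 4.5 and 9 deaths. Ten deaths would need about 333.
- **This is a secondary, exploratory grouping, and details belong in an analysis plan.** Covariate lists and sparse-event rules can indeed be left there. But the article itself fixes the method and threshold, and does not label the survival comparison exploratory.
- **A ban on p-values would go too far.** An exact rank test stays valid with few deaths. This stands.

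**Conclusion.** The concern holds in a limited form. The plan commits to a survivor versus non-survivor contrast and to multivariable regression on prognosis without securing any number of deaths. The expected count is about 2 at the unselected rate and roughly 2 to 10 with assumed sepsis enrichment. Even the high case of 18 supports no more than one covariate. The conclusion therefore does not depend on which assumption is chosen, although the counts do: the documents give neither the sepsis share nor sepsis mortality.

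The defect affects a secondary analysis. The comparison of cases with healthy controls is untouched, and the sepsis comparison has 30 events by design.

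**What to change.** In the Multi-Omic Data Analysis Plan:

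1. Restrict multivariable logistic regression, and ROC evaluation of selected biomarkers, to sepsis versus non-sepsis (30 versus 30), and replace the word prognosis with that outcome. Thirty events still allow only about three covariates at 10 per variable, so the model should stay small.
2. Label the 28-day survival comparison exploratory and mainly descriptive, and report the number of deaths with it.
3. If death is modelled or tested at all, use a single-predictor Firth-penalized logistic model or an exact rank test, and make no claim of a prognostic biomarker from it.

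The cost is a change of wording, with no extra patients, samples or assays. The sponsor gives up a confirmatory-sounding statement about mortality that the expected number of deaths could not support.

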## Method and Analysis

### Study Design

This protocol is designed as a prospective observational case–control study in patients who underwent cardiopulmonary bypass (CPB) due to cardiac surgery. Thirty healthy persons aged between 18 and 85, without digestive system disease, will be selected as the control group. The case group will include patients admitted to the intensive care unit (ICU) after cardiac surgery with CPB, which is performed by the Department of Cardiac Surgery of Peking Union Medical College Hospital. The patients enrolled should be divided into two groups according to their outcomes: one group of non-sepsis patients and the other group of sepsis patients after cardiac surgery. Sample collection will be terminated when each group receives 30 cases. These 60 cases will be regarded as the case group. Additionally, all the patients we observe will be further divided into survivors and non-survivors based on 28-days survival. Feces and blood samples will be obtained at certain time points (Figure 1).

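### If the 30 + 30 sepsis quota is followed, the pooled primary CPB-versus-healthy contrast after surgery reflects a 50% sepsis share set by design, not CPB patients in general

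*Protocol article*

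**What the plan says.** Under Study Design, patients are classified by what happens to them after surgery: "The patients enrolled should be divided into two groups according to their outcomes", septic and non-septic. The quota then sets both the stopping point and the composition of the case group: "Sample collection will be terminated when each group receives 30 cases. These 60 cases will be regarded as the case group". The comparator is defined in the same paragraph: "Thirty healthy persons aged between 18 and 85, without digestive system disease, will be selected as the control group".

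Grouping by Outcomes names the primary comparison: "The primary outcome is patients with cardiovascular surgery with CPB and healthy people". Septic versus non-septic and survivor versus non-survivor are listed there as secondary.

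The Multi-Omic Data Analysis Plan states that "a linear mixed-effect model will be used to assess the differences between the case group and the control group", at a two-sided 0.05 level. It also lists separate analyses by sepsis and by survival. For the case-control contrast it mentions no sepsis term, stratum or weight.

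The Introduction gives the aim in general terms: "This study will identify the variation in the gut microbiota and host metabolite profiles of patients after undergoing cardiac surgery with CPB". The Conclusion likewise speaks of CPB patients as a whole.

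Two other places describe enrolment without the quota. Recruitment stops at 60 cases, and the Discussion speaks of enrolling sixty patients and observing their outcomes. Under Sample Collection, cases are sampled at T1 (the day before surgery) and T2 (24–72 h after ICU admission), and controls once.

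**The concern.** An outcome quota suits the septic versus non-septic comparison, because it gives two equal groups. The same 60 patients are then reused, pooled, for a different question: how CPB patients differ from healthy people. The mean of the pooled group is the simple average of the septic and non-septic means. It equals the mean among CPB patients only if half of them become septic, or if septic and non-septic patients have the same mean.

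The primary effect at T2 therefore depends partly on a number chosen by the investigators. A feature that is abnormal only in septic patients can appear as a case-control difference and be described as typical after CPB. The Introduction wants to separate sepsis from a purely inflammatory response, and a pooled contrast blurs that distinction.

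The problem arises when the Study Design rule is followed exactly, so it is separate from the question of which stopping rule applies. Which rule applies does decide whether the problem occurs at all.

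**Working it through.** **Inputs from the article.** 30 septic + 30 non-septic = 60 cases, so the septic share is 30/60 = 50%. There are 30 controls. The test is two-sided at 0.05. The article gives no effect size, SD, power or named endpoint variable, so there is no sample-size figure to reproduce.

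**Inputs assumed.** The true sepsis incidence p after CPB is not given; 5 to 30% is used. One feature is examined at T2 with SD 1. Non-septic patients equal healthy people, and septic patients are shifted by d.

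**What is estimated.** With d₀ the non-septic and d₁ the septic difference from healthy:

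- Quota sample: 0.5·d₀ + 0.5·d₁
- CPB population: (1 − p)·d₀ + p·d₁
- With d₀ = 0, the ratio of the two is 0.5/p.

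**Rejection rates.** Simulation (20,000 runs, Welch t-test, 60 v 30) with d₀ = 0 and d₁ = 1 SD:

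| Septic share of the 60 | Expected difference | Ratio 0.5/p | Rejects |
|---|---|---|---|
| 50% (quota) | 0.50 SD | – | about 56% |
| 30% | 0.30 SD | 1.7 | about 24% |
| 20% | 0.20 SD | 2.5 | about 13% |
| 10% | 0.10 SD | 5 | about 7% |
| 5% | 0.05 SD | 10 | about 5% |

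For other septic shifts, the quota sample rejects in 19% (0.5 SD), 40% (0.8 SD) and 88% (1.5 SD) of runs. At a 20% share the figures are 7, 10 and 23%. With no shift, every version rejects about 5%.

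**When non-septic patients also differ.** With d₀ = 0.3 and d₁ = 1.0, the quota gives 0.65 SD. The population value is 0.37, 0.44 and 0.51 SD at p = 10, 20 and 30%. With d₀ = d₁ = 0.3 both give 0.30 and nothing is distorted.

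**Time points.** At T1 nobody has post-operative sepsis. With the shift at T2 only, a T1 contrast rejects about 5%. A case effect averaged over T1 and T2 rejects about 20–22% (assumed within-patient correlation 0 to 0.7). The 56% therefore belongs to a T2 contrast.

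**Could 30 + 30 arise without selection?** The chance that 60 consecutive patients include at least 30 septic is 0.0009 at p = 30% and 2 × 10⁻⁷ at p = 20%. Reaching 30 septic cases needs about 30/p patients: 100, 150 and 300 at 30, 20 and 10%. Unless incidence is near 50%, a 30/30 split comes from the quota.

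**Cost of weighting.** Standard error of the unweighted contrast: √(1/60 + 1/30) = 0.224 SD. Weighted by a known p: √(p²/30 + (1 − p)²/30 + 1/30) = 0.252, 0.246, 0.237 and 0.229 SD at p = 5, 10, 20 and 30%. Each stratum against controls (30 v 30): √(1/30 + 1/30) = 0.258 SD.

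**The case against.** **The quota is not stated everywhere.** Recruitment and the Discussion can both be read as 60 unselected patients followed forward. On that reading the distortion does not arise. This stands, so the point is conditional on the Study Design rule. That rule, however, is the only text that says what the 60 consist of.

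**Enrichment is deliberate and the sepsis comparison is planned.** This also stands: the quota does no harm to septic versus non-septic. With 30 v 30, a septic-only shift of 1 SD would be found there about 97% of the time (one feature, nominal 0.05), so such a signal would not go unnoticed. But that comparison does not show whether non-septic CPB patients differ from healthy people, and the primary claim needs that.

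**The planned model is a repeated-measures mixed model, not a T2 t-test.** Correct. The article does not say which time point carries the case-control effect, and an average over T1 and T2 would reject less often. At T1 the only concern is that cases are selected on a later outcome, which matters if the pre-operative profile predicts sepsis.

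**Weighting may be left to a fuller document.** Possibly. The point rests on what is stated: the quota and the pooled primary contrast.

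**Stronger readings to avoid.** A reader might infer that the type I error is inflated. It is not: if no CPB patient differs from healthy people, rejection stays at about 5%. Excess rejection of the null that the incidence-weighted CPB mean equals healthy requires non-septic patients to be shifted the opposite way by exactly p/(1 − p) of the septic shift (0.11, 0.25 and 0.43 SD at 10, 20 and 30% for 1 SD). Nothing in the article suggests this.

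A reader might also infer that non-septic versus healthy isolates the effect of CPB. It does not. The Introduction proposes that CPB leads to sepsis through bacterial translocation, so dropping septic patients conditions on a possible consequence of CPB. Non-septic patients also still differ from healthy people in heart disease, surgery and ICU care.

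**Conclusion.** The concern holds in conditional form. If the case group is filled as Study Design says, the unweighted T2 case-control contrast answers a question about a half-septic mixture rather than about CPB patients, and a septic-only difference could be reported as a general one. Under the assumed septic-only shift, the estimate is 1.7 to 5 times too large at incidences of 30 down to 10%. Incidence and shift are both assumptions, and the factor shrinks when non-septic patients differ too.

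The distortion vanishes if septic patients do not differ, if true incidence is near 50%, or if 60 unselected patients are taken. The first of these would contradict the study's own hypothesis. The fault lies in the estimand and in how a rejection would be interpreted. The septic versus non-septic comparison is unaffected.

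**What to change.** 1. Reconcile Study Design with Recruitment (and the Discussion): state whether enrolment stops at 60 patients or when both outcome groups hold 30.
2. If the quota stands, report septic versus healthy and non-septic versus healthy separately at T2, beside the primary contrast. These need no incidence figure. Describe them as differences between groups, not as the effect of CPB itself.
3. Give any pooled CPB-versus-healthy estimate at T2 with the two strata weighted by the sepsis share observed among all eligible consented patients. Otherwise limit its conclusion to the enriched sample.

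Cost: a tally of sepsis status in all eligible consented patients and some analysis wording; no extra patients or samples. The weighted estimate has a slightly larger standard error (about 0.23–0.25 against 0.224 SD, treating the share as known), and the separate contrasts rest on 30 v 30.
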